#### Exploratory Ordinal Outcome for Aim 3: Suicidal Ideation during the 10-day acute Trial Period

**Hypothesis 3b:** We expect that, among the adolescents who receive active sequential bilateral aTBS treatment, there will be an indirect relationship between cortical inhibition (as assessed by TMS-EEG N45, N100) and suicidal ideation (as assessed by the C-SSRS severity of ideation subscale) over the 10 day acute treatment trial.

An ordinal logistic regression model within a GEE analysis framework similar to that described above for Hypothesis 2b will be used here to examine the relationship between cortical inhibition (LIC1-100, N100 as a time-varying covariate) and C-SSRS severity of ideation subscale (as the response variable) over the 10-day acute treatment trial. A separate model will be implemented for each measure of TMS-EEG cortical inhibition. The same covariates specified in Hypothesis 2b will be included in the model for Hypothesis 3b. The parameter estimates (regression coefficients) will be interpreted from the solution for fixed effects in the GEE analysis. The adjusted odds ratio (i.e., odds of suicidal ideation from TMS-EEG cortical inhibition), and 95% confidence interval, will be estimated as part of the GEE model.

## **Sensitivity Analysis**

In this section we present a brief sensitivity analysis plan to address incomplete response patterns according to a missing not at random mechanism. First, we will follow the outcome-based model framework of Diggle and Kenward (1994) for longitudinal data with non-random missingness along with the model-based approach proposed in Carpenter et al. (2002) for modeling both the treatment response and the missing data process. That is, if deemed necessary, we will build longitudinal models for the data which includes a model for the dropout (or missing data) process so as to assess the sensitivity of the results about the dependence between dropout (or missingness) and treatment response. Additionally, if deemed necessary, we will consider implementing the semi-parametric shared parameter model approach as described in Tsonaka et al. (2009) to handle nonmonotone nonignorable missingness for mixed-effects models. A Pattern-Mixture Model will also be considered (if

necessary). The results from such (non-random dropout/missingness) models will then be compared with the results of the proposed standard methods (dropout or missing at random models) so as to assess the sensitivity of the results to the effect of dropouts (or incomplete response patterns according to a missing not at random mechanism).

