## 7 Statistical Plan

### 7.1 Sample Size Determination

#### Sample Size Estimation and Power Analysis for the Primary Aim of the Study

We established the sample size for the Primary Aim/Outcome/Hypothesis 1a (suicidal ideation over 10 days of acute sequential bilateral aTBS treatment) by incorporating a repeated measures design, with assumptions about potential participants (e.g., effect size/odds ratio), based on general guidance from a recent study that evaluated the effect of bilateral rTMS vs. sham stimulation on suicidal ideation in adult patients with treatment-resistant MDD. The results of the *a priori* sample size estimation and power analysis suggest that a sample size of 35 participants per group (N=70) achieves 80% power, at a 0.05 alpha level (two-tailed), to detect an overall odds ratio of 2.85 (sequential bilateral aTBS vs. Sham stimulation on lower-ordered intensity of suicidal ideation CSSR-S subscale scores—less suicidal ideation) in a 2 (between-subjects) group randomized design with 10 (within-subjects) repeated measurements of the primary ordinal outcome (suicidal ideation), when the proportion (or incident rate) of suicidal ideation from the sham group at the end of the 10-

day trial  $\geq 0.50$ , and the assumed within-subject correlation between observations (suicide ideation) on the same subject is  $\leq 0.50$  (0.50 was based on guidance from our preliminary TMS work). We note that the posited odds ratio of 2.85 for the current application is a bit more conservative than what was reported in the Weissman, et al. (2018) study of bilateral TMS vs. Sham stimulation on suicidal ideation in adult patients with treatment-resistant MDD (odds ratio=3.03).

We anticipate some dropouts (~10% based on treatment discontinuation results from our previous rTMS studies). Thus, ~80 participants will be enrolled to allow for this expected rate of attrition with the intent of capturing a range of evaluable data for 70 participants. The Power Analysis and Sample Size (PASS) 2019 software, version 14.0.15, was used to carry out the sample size and power analysis (PASS 2016, NCSS, Inc., Kaysville, Utah).

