### Primary Aim

#### Data Analysis Plan for Primary Aim 1 (Hypotheses 1a–1c)

##### Primary Outcome for Aim 1: Suicidal Ideation during the 10-day acute Trial Period

**Hypothesis 1a:** We expect 10 days of sequential bilateral aTBS will have greater efficacy for improving suicidal ideation in adolescents with MDD (as assessed by the C-SSRS severity of ideation subscale) over the 10-day acute treatment trial compared to sham stimulation.

Suicidal Ideation (as measured by the C-SSRS severity of ideation subscale) over the 10-day acute sequential bilateral aTBS trial period will be the primary ordinal outcome measure. The acute change over time (10 days) in Suicidal Ideation will be compared between the two treatment groups (sequential bilateral aTBS vs. sham stimulation) using an ordinal logistic regression model within a Generalized Estimating Equation (GEE) framework. The logistic model will contain fixed effects terms for treatment, time, treatment  $\times$  time interaction along with baseline C-SSRS severity of ideation subscale as a covariate. Age, sex, pubertal status, antidepressant medication status, and depression severity (CDRS-R total as a time-varying covariate) will also be included as covariates in the model. Simple treatment group effects in each time period will also be assessed. [see sensitivity analysis section below for missing not at random (MNAR) mechanism].

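### If a random-effects logit model serves as the MNAR check for Hypothesis 1a or 1b, comparing its odds ratio with the GEE odds ratio mixes a change of scale with the effect of dropout

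*Protocol*

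**What the plan says.** Protocol section 7.2 analyses Hypothesis 1a (C-SSRS severity of ideation over the 10 treatment days) "using an ordinal logistic regression model within a Generalized Estimating Equation (GEE) framework". The Statistical Methodology row of the Study Summary makes the odds ratio from that model the effect-size measure. Hypothesis 1b uses a similar ordinal GEE over the 12-month follow-up. The text for 1a directs the reader onward: "see sensitivity analysis section below for missing not at random (MNAR) mechanism".

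The Sensitivity Analysis part of section 7.2 names three routes:

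- an outcome-based model of the response together with the dropout process;
- a semi-parametric shared-parameter model, to be considered if deemed necessary, "to handle nonmonotone nonignorable missingness for mixed-effects models";
- a pattern-mixture model, also only if necessary.

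One rule then covers whichever models are fitted: "The results from such (non-random dropout/missingness) models will then be compared with the results of the proposed standard methods". A parenthesis describes those standard methods as the ones that assume dropout or missingness at random. For 1a and 1b, the standard method proposed in section 7.2 is the GEE. The section gives no effect scale for the comparison, no averaging over random effects, and no missing-at-random mixed model for these two hypotheses.

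**The concern.** The sensitivity analysis is meant to show whether informative dropout changes the treatment effect. For that, the two models should agree when dropout is ignorable, so that any difference can be attributed to the missingness model.

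A cumulative-logit GEE and a cumulative-logit model with subject random effects do not meet this condition. The first estimates a population-averaged odds ratio and the second a subject-specific one. With a logit link, these differ whenever there is a treatment effect and subjects vary, even with every rating observed. The subject-specific value lies further from 1.

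At stake is how the check is read. Harmless dropout can look like sensitivity, because the MNAR odds ratio comes out larger. Dropout that flatters the active arm can go unnoticed, because the change of scale pushes the MNAR odds ratio back towards the GEE value.

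**Working it through.** **Inputs from Protocol section 7.1.** The target is stated as "a sample size of 35 participants per group (N=70) achieves 80% power". The other inputs are: two-sided alpha 0.05; odds ratio 2.85; 10 ratings per subject; sham proportion 0.50 (stated as at least 0.50); within-subject correlation 0.50 (stated as at most 0.50); about 10% dropout.

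**The plan's own figure.** Active proportion: 2.85 / (1 + 2.85) = 0.7403. The pooled two-proportion formula for 0.50 against 0.7403 gives 63 per group with one measurement each. The repeated-measures factor is (1 + 9 × 0.5) / 10 = 0.55, and 63 × 0.55 = 34.65, so 35 per group, with power 80.5%. The stated sample size reproduces, which supports reading 2.85 as a population-averaged odds ratio.

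**Scale gap with no missing data.** Assume a random-intercept logit with standard deviation σ and a binary split of the scale. The marginal probability is p(η) = ∫ expit(η + σb) φ(b) db. Solve for η at p = 0.50 and at p = 0.7403; the subject-specific odds ratio is exp(η₁ − η₀). The protocol does not say on which scale its correlation is measured, so both readings are shown:

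- latent scale: σ² / (σ² + π²/3);
- observed scale, at p = 0.50: [∫ expit(σb)² φ(b) db − p²] / [p(1 − p)].

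| Within-subject correlation | σ | Subject-specific OR matching a marginal OR of 2.85 |
|---|---|---|
| 0.12 observed | 0.78 | 3.26 |
| 0.15 observed (0.20 latent) | 0.91 | 3.39 |
| 0.22 observed (0.30 latent) | 1.19 | 3.77 |
| 0.30 observed | 1.53 | 4.37 |
| 0.50 latent | 1.81 | 5.00 |
| 0.50 observed | 2.67 | 7.84 |

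The usual attenuation approximation at latent 0.50 gives exp(1.047 × √(1 + 0.346 × 3.29)) = exp(1.047 × 1.46) = 4.6, slightly below the integrated 5.0.

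**Ordinal check.** A six-category cumulative logit with latent correlation 0.50 was simulated with 4,000 subjects, 10 visits and no missing data. Subject-specific odds ratios of 4.6, 2.85 and 1.0 gave pooled marginal odds ratios of 2.91, 1.91 and 0.99. The gap is present for the ordinal outcome and absent at the null.

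**Masking.** At latent 0.50, a subject-specific odds ratio of 2.85 corresponds to a marginal odds ratio of about 1.97. A random-effects MNAR model returning 2.85 would look unchanged against a GEE value of 2.85, although on the GEE scale the effect had fallen to about 2.

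**Yardstick (assumed).** Let 10% drop out, count every active-arm dropout as not improved, and let sham dropouts resemble completers. The active proportion becomes 0.7403 × 0.90 = 0.6662, and the odds ratio is 0.6662 / 0.3338 = 2.00. At the ceiling correlation, the change of scale is about as large as this severe departure.

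**Hypothesis 1c.** With a log link and a random intercept, a subject-specific rate ratio of 0.70 integrates to a marginal rate ratio of 0.70. No gap arises.

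**The case against.** A reader might infer that the whole MNAR analysis is invalid, or that it cannot answer its question. The protocol does not support that reading.

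- **Optional model.** The shared-parameter model is one of three routes and is only to be considered if judged necessary. The outcome-based and pattern-mixture routes need not give subject-specific odds ratios. This stands, and it makes the point conditional.
- **Possibly meant for 1c.** The text ties the shared-parameter model to mixed-effects models, and among the Aim 1 analyses only 1c is called one. But 1a is sent to the same section, and the comparison rule draws no distinction between hypotheses, so use for 1a remains open.
- **The rule speaks of results, not odds ratios.** It sets no equality criterion or test, and a SAP could supply the scale. That is fair. However, the odds ratio is the effect measure the protocol names for 1a, and the comparator is written down. A SAP would have to add to or depart from it.
- **The ceiling overstates the gap.** The protocol gives 0.50 as an upper bound. The model also adjusts for baseline C-SSRS, time-varying CDRS-R, age, sex, pubertal status and medication status, which may lower the residual correlation. This stands; the lower rows of the table are the relevant ones if it does.
- **Direction and significance survive.** In 300 simulated complete-data trials (binary outcome, 40 per arm, 10 visits, latent correlation 0.50) the odds ratios were 2.87 and 4.96. Median z values were 3.41 and 3.48, and the two models agreed on 5% significance in 98.7% of trials. With half the random-intercept variance, the odds ratios were 2.72 and 3.64, with agreement in 99%. This stands. Only the comparison of odds-ratio size fails.

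**Conclusion.** The point holds in conditional form. If a shared-parameter or other random-effects logit model is used for Hypothesis 1a or 1b, the stated comparator is on a different scale. Neither a difference nor an agreement in odds-ratio size can then be read as sensitivity or robustness to dropout.

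For 1a the distortion runs from modest, if the residual correlation is low, to as large as a strong MNAR shift at the protocol's ceiling. These sizes assume a true marginal odds ratio of 2.85, a normal random intercept and complete data. The correlations of 0.12 to 0.22 are illustrative, since the protocol gives only the upper bound. For 1b the mechanism is the same, but the protocol gives no design odds ratio from which to size it.

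It would be wrong to conclude that the primary result or its type I error is compromised: the primary analysis does not depend on this comparison. Severity is minor.

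**What to change.** Amend the comparison sentence in the Sensitivity Analysis part of section 7.2. For Hypotheses 1a and 1b, either:

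1. compare any random-effects MNAR model with the same cumulative-logit mixed model fitted without the missingness link; or
2. average its treatment effect over the random effects before setting it beside the GEE odds ratio.

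Alternatively, carry out the pattern-mixture option already listed as delta-adjusted multiple imputation followed by the same ordinal GEE, so that both odds ratios are population-averaged.

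The cost is a sentence in the protocol and SAP and one extra model fit or imputation run. The delta values or the averaging step must be fixed in advance. No new data are needed, and the primary analysis stays as it is.

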### 7.3 Subject Population(s) for Analysis

- All-treated population: Any subject randomized into the study that received at least one exposure (treatment) from the study device.

## 8 Safety and Adverse Events

**Table 5. Reporting Time Frames**

| Reportable Events                                                   | DSMB
(Time
Frame)                                                                | FDA
(Time
Frame)                                                   | IRB
(Time
Frame)                                                   | OHRP
(Time
Frame)                     |
|-----------------------------------------------------------------------------------|--------------------------------------------------------------------------------------------------------|------------------------------------------------------------------------------------------|------------------------------------------------------------------------------------------|-------------------------------------------------------------|
| IRB/DSMB/OHRP/FDA
Suspensions or
Termination                       | Within 3
business days
of receipt                                                       | Within 3
business days
of receipt                                         | Within 3
business days
of receipt                                         | Within 3
business days
of receipt            |
| Deaths related to study
participation                                  | Within 5
business
days)                                                                 | Within 5
business
days)                                                   | Within 5
business
days)                                                   | Not
applicable                                   |
| Unexpected Serious
Adverse Events Related
to Study Participation   | Within 5
business days
upon
notification                                            | Within 5
business days
upon
notification                              | Within 5
business days
upon
notification                              | Not
applicable                                   |
| Expected Serious Adverse
Events Related to Study
Participation     | Within 5
business days
upon
notification                                            | Within 5
business days
upon
notification                              | Within 5
business days
upon
notification                              | Not
applicable                                   |
| Unexpected/Unrelated
and Expected/Unrelated
Serious Adverse Events | Filed in the
triannual
DSMB
progress
reports                                    | Filed with
annual
progress
reports                                    | Filed with
annual
progress
reports                                    | Not
applicable                                   |
| Unanticipated Adverse
Device Effect                                    | Within 5
business days
upon
notification                                            | Within 5
business days
upon
notification                              | Within 5
business days
upon
notification                              | Not
applicable                                   |
| Unanticipated Problems
Involving Risks to
Subjects or Others       | Within 5
business days
upon
notification                                            | Within 5
business days
upon
notification                              | Within 5
business days
upon
notification                              | Within 5
business days
upon
notification |
| Serious Or Continuing
Noncompliance                                    | Within 5
business days
upon
notification                                            | Within 5
business days
upon
notification                              | Within 5
business days
upon
notification                              | Within 5
business days
upon
notification |
| Adverse Events                                                             | Expected and
unrelated are
filed in the
triannual
DSMB
progress
reports | Expected and
unrelated are
filed with
annual
progress
reports | Expected and
unrelated are
filed with
annual
progress
reports | Not
applicable                                   |

| Protocol Violations | Annual progress reports                  | Annual progress reports                  | Annual progress reports                  | Not applicable |
|----------------------------|-------------------------------------------------|-------------------------------------------------|-------------------------------------------------|-----------------------|
| Pregnancy           | Within 5 business days upon notification | Within 5 business days upon notification | Within 5 business days upon notification | Not applicable |

Note – Some Adverse Events represent Unanticipated Problems that are required to be reported to OHRP (see: <https://www.hhs.gov/ohrp/regulations-and-policy/guidance/reviewing-unanticipated-problems/index.html>)

All adverse events occurring during the study, including those not meeting the criteria of an Unanticipated Adverse Device Effect (UADE) will be recorded on the appropriate case report form. Reporting time frames for the DSMB, FDA, and IRB are summarized in table 5. Expected clinical adverse events and anticipated adverse device effects include pain or discomfort under the treatment coil, eye pain, facial pain, facial numbness, toothache pain, skin pain, facial muscle twitching, blurred vision, seizures, cardiogenic syncope, and worsening mood symptoms. The DSMB will review all adverse events (expected and unexpected) in DSMB data reports submitted tri-annually. Unanticipated Adverse Device Effects (UADEs) will be reported to the DSMB, FDA, and IRB immediately (as noted in Table 5). Records of these events will be maintained and reports submitted to the FDA and IRB according to the regulatory requirements. Expected clinical adverse events and nonsignificant (not serious) clinical adverse events will be reported annually. Expected clinical adverse events and anticipated adverse device effects are those listed in Section 1.5.2.

Any pregnancy detected during the acute 10 day treatment course or a pregnancy that may have been present during the acute 10 day treatment course (based on estimated date of conception in consultation with the subject's clinical obstetrician) will be reported within 5 business days to the IRB, DSMB, and FDA. If a pregnancy is detected during the acute 10 day treatment course no further investigational treatments will be delivered but the patient will be followed for 12 months as per the study protocol. The pregnancy outcome will be documented.

## 8.1 Definitions

### Unanticipated Adverse Device Effect (UADE)

A UADE is any serious adverse effect on health or safety or any life-threatening problem or death caused by, or associated with, a device if that effect, problem or death was not previously identified in nature, severity, or degree of incidence in the investigational plan or IDE application (including a supplementary plan or application), or any other unanticipated serious problem associated with a device that relates to the rights, safety, or welfare of subjects.

**Adverse Effect (Event)**

Any untoward medical occurrence in a subject involved in clinical study of an investigational device; regardless of the causal relationship of the problem with the device or, if applicable, other study related treatment(s). Adverse events will be reported to the DSMB tri-annually.

**Associated with the investigational device:** There is a reasonable possibility that the adverse effect may have been caused by the investigational device. “Reasonable possibility” will be determined based on the PIs experience and relevant literature. These determinations will be reviewed with the study medical monitor, [name]) three times per year.

**Life-threatening adverse effect:** Any adverse effect that places the subject, in the view of either the investigator or the sponsor, at immediate risk of death from the effect **as it occurred**. It does not include a reaction that, had it occurred in a more severe form, might have caused death.

**Serious adverse effect:** An adverse effect is considered “serious” if, in the view of either the investigator or the sponsor, it results in any of the following outcomes:

- death
- a life-threatening AE
- inpatient hospitalization or prolongation of existing hospitalization
- a persistent or significant disability/incapacity
- a congenital anomaly/birth defect.

**Unanticipated adverse effect:** Any adverse effect, the nature, specificity, severity, or frequency of which is not consistent with the risk information in the clinical study protocol or elsewhere in the current IDE application.

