| Adverse events                                                                                                                                 | Subjects will be evaluated for adverse events at each visit. Serious adverse events (SAEs) will be reported as they occur to the Mayo Clinic IRB and USA FDA (as per regulations). Systematic data collection focused on adverse events will include the Pediatric Adverse Event Rating Scale and Physical Symptom Checklist.                |
| Auditory thresholds                                                                                                                            | Subjects will undergo audiometry testing at baseline and upon completion of 10 days of sequential bilateral aTBS.                                                                                                                                                                                                                                               |
| Beck Depression Inventory-II                                                                                                                   | This is a validated, 21-item, self-report measure with a range of 0-63. Collected at screening, baseline, weekly during the 10-day treatment and then monthly for 1 year follow-up period.                                                                                                                                                        |
| Brief Affective Neuroscience Personality Scale                                                                                                 | This is a validated 33-item, self-report measure collected at screening only to assess behavioral characteristics in 6 affective neurobiological systems (play, seek, care, fear, anger, and sadness)                                                                                                                                                           |

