#### Causality and severity assessment

The sponsor-investigator will promptly review documented adverse effects and abnormal test findings to determine 1) if the abnormal test finding should be classified as an adverse effect; 2) if there is a reasonable possibility that the adverse effect was caused by the investigational device or other study treatments; and 3) if the adverse effect meets the criteria for a serious adverse effect.

If the sponsor-investigator's final determination of causality is "unknown and of questionable relationship to the investigational device or other study treatments," the adverse effect will be classified as associated with the use of the investigational device or other study treatments for reporting purposes. If the sponsor-investigator's final determination of causality is "unknown but not related to the investigational device or other study treatments," this determination and the rationale for the determination will be documented in the respective subject's case history.

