##### ***Study Stopping Rules***

In order to ensure that subjects are not exposed to risks across the study and that risks are evaluated the follow are study stopping rules. **These stopping rules apply to the two-week period when subjects are receiving the study intervention (active or sham sequential**

**bilateral aTBS). These rules do not apply to subjects in the naturalistic 1-year follow-up portion of the study.** There are no pre-determined stopping rules for events that take place during the follow up-period as suicide attempts and psychiatric hospitalizations are expected to be common events. Adverse events that occur while subjects are in the follow up period will be tracked during the long term naturalistic follow up. The study team will be evaluating the expectedness and relatedness of these events; the IRB, DSMB, FDA will provide oversight of these determinations. AEs and SAEs will be reported and reviewed by the DSMB in the data reports according to the timeframes delineated in Section 8, Table 5.

- i. Two subjects who experience seizure(s).
- ii. One or more subject(s) who experiences status epilepticus.
- iii. One or more subject(s) who attempts or dies by suicide.
- iv. Two or more Serious Adverse Events--related to the study intervention and occurring within the 2-week treatment period--in one or more subjects.

In the event these study stopping rules are met, enrollment of new subjects will cease, but all study activities will continue for enrolled subjects. The PI will consult with the DSMB and the FDA within 10 business days upon initial notice of meeting stopping rules.

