## **8.6 Medical Monitoring**

It is the responsibility of the sponsor-investigator to oversee the safety of the study. This safety monitoring will include careful assessment and appropriate reporting of adverse events as noted above, as well as the construction and implementation of a site data and safety-monitoring plan (see Section 10 Auditing, Monitoring and Inspecting). Medical monitoring will include a regular assessment of the number and type of serious adverse events. The study has an internal (Mayo Clinic) medical monitor ([name]). The medical monitor will be blinded to study intervention. The medical monitor will be consulted if a serious adverse device effect occurs to determine if the blind should be broken for the safety of the participant. The medical monitor will assist with the evaluation of adverse effects with respect to the reasonable possibility that the adverse effect may have been caused by the investigational device. "Reasonable possibility" will be determined based on the PI's experience and relevant literature. These determinations will be reviewed with the study medical monitor ([name]) three times per year.

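### Deaths and SAEs that the sponsor-investigator judges unrelated wait for periodic reports without a prompt independent check, and the protocol's reporting time frames contradict each other

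*Protocol*

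**What the plan says.** **Who decides.** Section 8.1 (Associated with the investigational device) says that reasonable possibility of causation "will be determined based on the PIs experience and relevant literature". Section 8.2 (Causality and severity assessment) gives the sponsor-investigator the task of deciding "if there is a reasonable possibility that the adverse effect was caused by the investigational device or other study treatments". Section 8.5 shows that investigator and sponsor are one role.

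**Who checks.** Section 8.1 continues: "These determinations will be reviewed with the study medical monitor". Section 8.6 repeats the interval as "three times per year".

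**What the decision controls.** In Table 5 the row "Deaths related to study participation" and the two rows for related SAEs carry a limit of 5 business days to the DSMB, FDA and IRB. The row "Unexpected/Unrelated and Expected/Unrelated Serious Adverse Events" goes to the DSMB triannually and to the FDA and IRB annually. Study stopping rule iv in Section 8.5 counts "Two or more Serious Adverse Events--related to the study intervention and occurring within the 2-week treatment period--in one or more subjects".

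**What other passages say.** Table 4 (Section 6.4, adverse events row) says, with a reference to regulations but no condition on relatedness: "Serious adverse events (SAEs) will be reported as they occur to the Mayo Clinic IRB and USA FDA (as per regulations". Section 8.1 (Hospitalization) makes UADE reporting the default for an event leading to admission, but exempts admissions for the target disease unless the investigator judges them a worsening or an increase in frequency. For UADEs, Table 5 sets 5 business days to the DSMB and FDA, while Section 8.3 sets 10 working days.

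**The concern.** One person's causality judgement selects between a 5-business-day report and a periodic one, and the only scheduled second opinion comes about every four months. In suicidal adolescents with depression, psychiatric admissions and late deaths are easily attributed to the illness. If such an event were wrongly and firmly called unrelated, no expedited report would follow under Table 5. During the treatment period the event would also not count towards rule iv. New subjects could then start before the DSMB, the monitor, the FDA or the IRB had a stated occasion to question the call.

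Separately, staff handling one SAE could find two or three different time frames in the same protocol, depending on where they look.

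**Working it through.** The plan states no figure to reproduce, so the check sets the passages side by side and then does a small calculation.

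**Step 1: which route does an event judged unrelated take?**
- *Death:* Table 5 names only deaths related to participation. Death is a seriousness criterion in Section 8.1, so an unrelated death falls into the unrelated-SAE row.
- *Other SAE:* the unrelated-SAE row applies directly.
- *UADE row (5 business days):* the definition needs an effect caused by or associated with the device and not previously identified. Suicidal behaviour and clinical deterioration are listed risks in Section 1.5.2.
- *Unanticipated-problem row (5 business days):* the event must be possibly related and not part of an underlying disease.
- *Hospitalisation:* it defaults to UADE reporting, but the target-disease exemption is applied by the investigator.
- *Doubtful causality:* Section 8.2 treats a questionable relationship as associated for reporting. Only a firm finding of no relationship leaves the fast route, and Section 8.2 then asks only that it be documented in the case history.

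**Step 2: is there a prompt check?** Sections 8.4 and 8.6 bring in the medical monitor ad hoc about unblinding, once there is a serious adverse device effect, so attribution has already been made. No other immediate review by the monitor is stated.

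**Step 3: what stops enrolment regardless of relatedness?** In the two-week treatment period, rule i (seizures in two subjects), rule ii (status epilepticus) and rule iii (a suicide attempt or death by suicide) carry no relatedness condition. Meeting one halts new enrolment, with DSMB and FDA consultation within 10 business days. Section 1.5.2 also has any seizure reported. What remains is:
- treatment-period SAEs outside rules i to iii that are firmly judged unrelated, which also drop out of rule iv;
- deaths and SAEs judged unrelated in the 12-month follow-up, where no study stopping rule applies.

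**Step 4: length of the gap**
- Monitor and DSMB: 12 months / 3 = up to about 4 months.
- FDA and IRB under Table 5: up to about 12 months.

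**Step 5: subjects starting in a gap.** Inputs: 80 subjects and 5 years (Study Summary); about 13 months of participation (Section 1.6); 100 enrolled to reach 80 (Section 4). No accrual period is stated, so even accrual is assumed. If the last subject completes within the study, accrual lasts at most 60 − 13 = 47 months.

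Formula: subjects = N / accrual months × gap.

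| Assumption | Per month | 4-month gap | 12-month gap |
|---|---|---|---|
| 80 over 60 months | 1.33 | 5.3 | 16.0 |
| 80 over 47 months | 1.70 | 6.8 | 20.4 |
| 100 over 47 months | 2.13 | 8.5 | 25.5 |

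The ranges are about 5 to 9 and 16 to 26. With 1:1 allocation, about half would receive active stimulation.

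**The case against.** The strongest reply is that the worst events are already covered. A reader might infer that a suicide or attempt during treatment could be called unrelated and pass unnoticed while enrolment goes on. The protocol does not support that, because rule iii applies whatever the causality call. A reader might also infer that an unrelated call in follow-up disables a stopping rule. It cannot: Section 8.5 limits the study stopping rules to the treatment period, and explains that attempts and psychiatric admissions are expected to be common afterwards.

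Further points stand in part:
- Doubt about causality defaults to the fast route, and hospitalisation defaults to UADE reporting. These narrow the gap but leave firm unrelated calls and exempted admissions, which rest on the investigator's judgement.
- Section 8.5 gives the IRB, DSMB and FDA oversight of relatedness in follow-up. The DSMB receives these events on Table 5's time frames, so its oversight inherits the delay.
- Section 8.6 says that the monitor assists with evaluating adverse effects. That does not exclude earlier involvement, but the only timing given for reviewing these calls is three times a year.
- Table 4's reference to regulations may be meant to defer to Table 5, which Section 8 calls a summary of the reporting time frames. That softens the contradiction, but the sentence states no relatedness condition.
- Section 8.3 speaks of reporting the results of an evaluation, so it could describe a second step after Table 5's report. The protocol does not say so.

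**Conclusion.** The point holds in a limited form and should be corrected. For treatment-period SAEs outside rules i to iii that are firmly judged unrelated, and for deaths and SAEs so judged in follow-up, Table 5 provides no expedited report, and no prompt independent review of the call is stated. The delay is up to about 4 months for the DSMB and monitor. The 12 months for the FDA and IRB holds only if Table 5 prevails over Table 4. The events are still recorded and eventually reported, so this is a delay and not a loss.

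The 5 to 9 and 16 to 26 subjects rest on assumed even accrual. They count subjects starting in a gap, in both arms, and are not an estimate of harm. They do not apply to events under rules i to iii.

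The disagreement among Table 4, Table 5, the hospitalisation text in Section 8.1 and Section 8.3 needs reconciling whatever view is taken of the relatedness check.

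**What to change.** 1. In Table 5, widen the row for related deaths to all deaths.
2. State in Sections 8.1 and 8.6 that the existing blinded medical monitor reviews the relatedness call for every death and every treatment-period SAE within Table 5's 5-business-day clock. Keep the review three times a year as a second look.
3. Reconcile Table 4, Table 5, the hospitalisation paragraph in Section 8.1 and the UADE timing in Section 8.3 into one set of time frames, and have the other passages refer to it.

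The cost is amendment wording plus a few extra short reviews and reports. It needs no new staff, and it leaves the treatment and the stopping rules unchanged.
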